## Abstract

**Background::**

Rheumatoid arthritis is a kind of chronic crippling disease, the condition is complex, the course of the disease is repeated, seriously affecting the quality of life of patients. Adverse reactions and drug resistance associated with conventional treatment can no longer meet the clinical need. Therefore, complementary and alternative therapies need to be explored. The evidence shows that silver needle therapy has advantages in the treatment of rheumatoid arthritis, but there is a lack of standard clinical studies to verify this conclusion.

**Methods::**

This is a prospective randomized controlled trial to study the efficacy and safety of silver needles in the treatment of rheumatoid arthritis. Approved by the Clinical Research Ethics Committee of our hospital. The patients are randomly divided into a treatment group (silver needle treatment group) or control group (routine western medicine treatment group). The patients are followed up for 2 months after 4 weeks of treatment. Observation indicators include: TCM symptom score, HAQDI score, DAS-28 score, laboratory indicators, adverse reactions and so on. Data will be analyzed using the statistical software package SPSS version 18.0 (Chicago, IL).

**Discussion::**

This study will evaluate the clinical efficacy of a silver needle in the treatment of rheumatoid arthritis. The results of this study will provide a reliable reference for the clinical use of a silver needle in the treatment of rheumatoid arthritis.

**Trial registration::**

OSF Registration number: DOI 10.17605/OSF.IO/4X5QB

## Introduction

1

Rheumatoid arthritis (RA) is the most common inflammatory arthritis. It is a chronic autoimmune disease characterized by symmetrical, persistent synovitis and destructive polyarthritis.^[1]^ According to 2010 data, the prevalence of RA accounts with 0.24% of the global population.^[2]^ In the United States, the annual loss caused by RA is more than $1 billion.^[3]^ RA is more common in women, and the risk of RA in women is about 3 times higher than that in men. The disease can occur at any age, the peak of incidence is between 30 and 50 years old, and the incidence increases with age, with the highest in women over 65 years old.^[4]^ RA is characterized by symmetrical multi-joint swelling and pain in the hand, wrist, foot and so on. The pathological changes are synovitis and pannus formation of joints, which lead to articular cartilage and bone erosion, joint deformities and loss of function, which is one of the main causes of disability.^[5]^

Rheumatoid arthritis is a disabled chronic disease, the condition is complex, the course of the disease is repeated, there is no specific treatment. At present, the mainstream management schemes for RA include nonsteroidal anti-inflammatory drugs (NSAIDs), conventional synthetic disease modifying anti-rheumatic drugs (csDMARDs), biological disease modifying anti-rheumatic drugs (bDMARDs), target synthetic disease modifying anti-rheumatic drugs (tsDMARDs), glucocorticoids and botanical drugs modified by modification.^[6]^ Most patients can achieve clinical remission after treatment, but there are still some patients who are easy to develop into refractory RA, and almost need to take drugs for life. In addition, the drugs for the treatment of RA not only delay the disease, but also bring great adverse reactions, which are difficult for patients to tolerate both financially and physically.^[7,8]^ Therefore, it is particularly important to seek safe and reliable complementary replacement therapy.

As a traditional Chinese medicine therapy, acupuncture plays an important role in many diseases.^[9]^ Silver needle therapy is similar to traditional acupuncture therapy, but there are some differences. Silver needles are not placed on acupoints, but on muscles, tendons and the fascia, heated by special machines to eliminate aseptic inflammation and relieve pain.^[10]^ Clinical studies have confirmed that silver needle can eliminate aseptic inflammation, improve blood circulation and relieve muscle spasm.^[11]^ The mechanism of silver needle therapy is similar to that of moxibustion, but moxibustion is heated by burning cotton balls and cannot control the temperature, while silver needles are heated by special equipment and the temperature can be set according to the patient's feedback.^[12]^ Silver needle therapy has achieved good results in low back pain, knee arthritis, ankylosing spondylitis and other diseases.^[12–14]^ However, there is a lack of clinical research on the efficacy and safety of silver needle therapy in the treatment of rheumatoid arthritis. Therefore, we intend to use this randomized controlled trial to evaluate the efficacy and safety of silver needle therapy in the treatment of rheumatoid arthritis.

## Materials and methods

2

### Study design

2.1

This is a prospective randomized controlled trial to study the clinical efficacy of silver needle therapy in the treatment of rheumatoid arthritis. This study will follow the comprehensive trial reporting standard.^[15]^ The flow chart is shown in Figure 1.

**Figure 1 F1:**
[figure not shown]
Flow diagram.

### Ethics and registration

2.2

This research scheme is in line with the Helsinki Declaration and has been reviewed by the Clinical Research Ethics Committee of our hospital. This lab is registered at OSF (registration number: DOI 10.17605/OSF.IO/4X5QB). Before being randomly divided into groups, all patients are required to sign an informed consent form, and they can choose whether to continue the trial or discontinue at any time.

### Sample size

2.3

The calculation of sample size is based on treatment, the mean value and standard deviation of TCM syndrome score. According to the results of the pilot study, the experimental group is 13.32 ± 4.30, and that of the control group is 15.83 ± 3.82. Set α = 0.025, one-sided test, β = 0.20. Calculated by PASS15.0 software, each group needs 43 participants, the estimated withdrawal rate is 20%, and each group will include 54 participants.

### Patients

2.4

Inclusion criteria:

1.meet the diagnostic criteria of rheumatoid arthritis (refer to RA diagnostic criteria of ACR in 2010 and the EULAR^[16]^);2.Age 18–70 years old, Rheumatoid Arthritis Disease Activity Score^[17]^ DAS-28 > 3.2, and in the active stage of the disease;3.Patients who do not take related drugs or other treatment within one month;4.Patients with strong compliance and signed informed consent.

Exclusion criteria:

1.Accompanied with important organ injury or malignant tumors, infectious diseases, blood system diseases;2.Accompanied with other rheumatic diseases;3.Pregnant and lactating women;4.In the late stage of rheumatoid arthritis, severely deformed joints caused by disability, life cannot take care of themselves;5.Allergic to the drugs used in this study.

### Study design

2.5

Eligible participants are randomly assigned to either the treatment group or the control group in a 1:1 ratio using a central-network-based randomization tool. Random sequences are generated by SAS 9.3 software (SAS Institute, Cary, NC, USA) by independent statisticians who do not participate in the implementation of the experiment or statistical analysis. The clinical research coordinator enters participants’ information on the tablet and is given a random number. The research assistant gets the allocation of participants from the computer. Throughout the study, the research assistant is responsible for screening, recruiting participants, and assigning random numbers to participants who had been included. Given the operational nature of the intervention, participants and operators may be aware of random allocation. However, the evaluators of research results and the statisticians of data statistics and analysis do not know about the distribution.

### Intervention measures

2.6

1.Treatment Group (silver needle treatment):a)Mark the tenderness point on the skin according to the pain site of the patient, which can be located on the muscle bundle, fascia, fascia or tendon. The needle point is determined by the central pain point, and the interval between each needle point is 1.0 cm – 2.0 cm. Finally, the needle point covers the whole painful area.b)After disinfection, 0.5% lidocaine is injected into the local anesthesia according to the needle point. Then insert the silver needle vertically or obliquely (the special silver needles which are 17 cm lengths of the needle body and 1 mm in diameter) into the needle point, usually through muscle or fascia attached to the bone surface or synovium. The patient will have soreness or swelling, indicating the correct position of the silver needle.c)Then the silver needle (ASTRONANTICS IN GOAL DIRECTION MED TECH Co., LTD., Shanxi, China) is connected to a special machine (YW-L1000; ASTRONANTICS IN GOAL DIRECTION MED TECH Co., LTD., Shanxi, China) and sets the heating temperature to ensure that the temperature of the silver needle entering the skin is about 42 °C for 25 min, often asking the patient how he feels to prevent scalds.d)After the needle is cooled, pull out the silver needle, disinfect the needle eye, wrap it with aseptic gauze, and do not touch water within 3 days. Once a week for 4 weeks.2.the control group (conventional western medicine treatment): Celecoxib capsule (Pfizer Pharmaceutical Co., Ltd., STATE MEDICAL PERMITMENT No J20140072), 0.2 g / time, once a day; methotrexate tablets (Shanghai Xinyi Pharmaceutical Co., Ltd., STATE MEDICAL PERMITMENT No H3102064), 10 mg/, once a week; leflunomide tablets (Jiangsu Yabang Epson Pharmaceutical Co., Ltd., STATE MEDICAL PERMITMENT No H20080420) 20 mg/, once a day. The patients are treated continuously for 4 weeks.

### Evaluation criteria and judgment of curative effect

2.7

1.TCM syndrome score: refer to the guiding principles of Clinical Research of New Drugs of Traditional Chinese Medicine (trial).^[18]^ The main symptoms and signs (including joint pain, joint swelling, limitation of joint activity, waist and knee soreness, fear of cold and cold, morning stiffness) are evaluated, and the scores are 0, 2, 4 and 6 respectively according to the severity, and the cumulative total score is the total score. The higher the total score, the more serious the illness.2.The Health Assessment Questionnaire Disability Index (HAQDI).^[19]^ According to the difficulty of completing 8 life-related actions (including dressing and grooming, getting up, eating, walking, personal hygiene, touching, grasping, activities, etc.), they are divided into 4 grades, corresponding to 0, 1, 2 and 3 points respectively. The HAQDI value is calculated by accumulating the 8 scores and calculating the average value. The higher the score is, the worse the quality of life is.

1.DAS-28 score ^[17]^:a)①DAS-28 score > 5.1 indicates high disease activity;b)②3.2 < DAS-28 score ≤ 5.1 indicates moderate disease activity;c)③2.6 < DAS-28 score ≤ 3.2 indicates low disease activity;d)④DAS-28 score ≤ 2.6 indicates basic remission of the disease.2.Laboratory examination: including serum calcium ion (Ca^2+^), ESR, hs-CRP, RF level.3.Adverse reactions: discomfort related to treatment occurred during treatment.

The above observation indexes are collected on the day before and after treatment. All patients are followed up for 2 months, and the data are collected according to the same standard in the first and second month.

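### The only safety outcome counts treatment-related discomfort during treatment, which omits other events and conflicts with the follow-up collection in the same section

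*Protocol article*

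**What the plan says.** The abstract and the Introduction of the protocol article both name safety, beside efficacy, as what the trial evaluates. The definition is one line in section 2.7: "Adverse reactions: discomfort related to treatment occurred during treatment". It is the last item in that section's list of outcomes, after the symptom score, HAQDI, DAS-28 and the laboratory tests.

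Directly after the list comes the schedule: "The above observation indexes are collected on the day before and after treatment". It continues: "All patients are followed up for 2 months, and the data are collected according to the same standard in the first and second month". The abstract places this follow-up after the treatment period: "The patients are followed up for 2 months after 4 weeks of treatment".

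Section 2.6 gives the treatment periods. The needle arm is treated "Once a week for 4 weeks". For the drug arm it says: "The patients are treated continuously for 4 weeks".

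Section 2.5 (on randomisation and blinding) states that "participants and operators may be aware of random allocation". It adds that outcome evaluators and statisticians are kept unaware of the allocation.

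The laboratory item reads: "Laboratory examination: including serum calcium ion (Ca^2+^), ESR, hs-CRP, RF level".

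**The concern.** An event must pass three filters before it counts: it must be a discomfort, it must be related to treatment, and it must occur during treatment. Each filter removes something that a safety comparison normally needs.

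- **Relatedness** turns a count of what happened into a count of what someone attributed to the intervention. In a trial where patients and operators may know the arm, that attribution can differ between arms for reasons other than harm.
- **Discomfort** limits the outcome to what the patient feels. An abnormality found without symptoms does not qualify.
- **During treatment** excludes an event that first appears in the two months of follow-up. Yet the next sentences of the section collect the same indexes at that time.

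Two analysts who follow different sentences of section 2.7 could therefore report different adverse-event rates from the same patients. The efficacy comparison is not touched. What is at stake is whether the trial can answer the safety half of its question.

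**Working it through.** The article gives no figure for safety: no expected event rate, and no hypothesis or power. Its sample size rests on the TCM syndrome score (section 2.3), and this point does not depend on it. The check is mainly a comparison of texts, with one piece of arithmetic.

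**1. Definition against schedule (both in section 2.7).** Adverse reactions belong to the list to which the schedule refers. The schedule collects the list before treatment, after treatment, and at months 1 and 2. The definition admits only events arising during treatment, so an event that starts in follow-up is inside the schedule and outside the definition.

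**2. Share of observed time that the definition covers.**

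- Treatment period: 4 weeks × 7 = 28 days (section 2.6, both arms).
- Follow-up: 2 months (abstract and section 2.7), taken as about 60 days. This is an assumption.
- Share = treatment days / (treatment days + follow-up days) = 28 / (28 + 60) = 28/88 = 31.8%, about 32%.
- Sensitivity: with 56 days (8 weeks), 28/84 = 33.3%; with 62 days, 28/90 = 31.1%. The result stays between 31% and 33%.

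About two thirds of the observed time therefore falls under the schedule but outside the definition.

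**3. Treatment window by arm.** The needle arm has four weekly sessions over 4 weeks; the drug arm has 4 weeks of continuous treatment. The nominal window is 28 days in each, a ratio of 28/28 = 1.0. The text does not say whether the days between sessions, or after the last one, belong to the treatment period. If the needle window closed at the fourth session, with the first on day 0, it would be 21 days and the ratio 21/28 = 0.75. The article does not state that reading.

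**4. Who judges relatedness.** Section 2.5 blinds the evaluators but not the patients or operators. No section assigns the causality judgement. The outcome also starts from what the patient reports. In the needle arm, section 2.6 treats aching or a swollen feeling on insertion as a sign of correct placement. The same sensation could thus be filed as good technique or as a related discomfort, a choice that exists in one arm only.

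**5. Non-symptomatic events.** The tests named are Ca2+, ESR, hs-CRP and RF. No liver, renal or blood-count measure is named, although the control arm takes three systemic drugs. Even if more tests are done, an abnormality without symptoms is not a discomfort and would not count.

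**6. Weight of single events.** With 54 patients per arm (section 2.3), moving one patient in or out of the count shifts that arm's rate by 1/54 = 1.9 percentage points. Three patients shift it by 3/54 = 5.6 points. The number of events actually affected cannot be computed, because no event rate is given.

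**The case against.** The best defence is that this is a condensed article. Elicitation of events, grading of causality and reporting of serious events commonly sit in the full protocol, the case report form or the analysis plan, and their absence here is no fault. That stands. The point rests only on the definition that the article does print, and on its clash with the sentences that follow it.

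A second defence is that the schedule sentence is generic and provides for collection at months 1 and 2, so later events are not plainly dropped. This stands in part. A reader might infer that follow-up contributes no adverse events at all; the text does not establish that, because it also says that the data are collected then. What is shown is a conflict. If the definition governs, new events in follow-up are lost; if the schedule governs, the definition is wrong. One of the two has to change.

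A reader might also infer that the arms have unequal observation windows, even 4 × 25 = 100 minutes of needle heating against 28 days on drugs. The documents do not support this. Nothing restricts the treatment period to session time, section 2.6 lists several days of care after needle removal among the treatment steps, and both arms have 4 weeks of treatment and the same follow-up. Only the lack of clarity about days between and after sessions remains.

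Nor does the article show that attribution is unblinded. Evaluators are blinded, and if they alone judge relatedness the risk is smaller. As no one is named for that task, bias is a risk and not a demonstrated fact.

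Finally, the laboratory list opens with a word that leaves it non-exhaustive, so other tests may be done. This limits the laboratory point to the tests that are named.

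**Conclusion.** The point holds in a limited form. The printed safety outcome omits events judged unrelated and events without symptoms. Its restriction to the treatment period contradicts the collection at months 1 and 2 in the same section. The definition covers about 32% of observed time (28 of 88 days), on the assumption that 2 months is about 60 days; the share is 31% to 33% for any reasonable length. The relatedness filter is open to bias, but the article does not show that bias occurs. Unequal windows between the arms are not shown; the treatment period is only left unclear around the weekly sessions. The effect on event counts cannot be quantified from the document. Efficacy conclusions are unaffected, and the correction is cheap.

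**What to change.** Rewrite the safety item in section 2.7 so that definition and schedule agree:

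- Record any untoward medical event, whatever its suspected cause, from randomisation to the month-2 visit. This also settles the days between and after sessions.
- Elicit events in the same way in both arms at the visits that already exist.
- Compare the arms on the number of patients with at least one event.
- Report relatedness as a secondary descriptor, and state who judges it and whether that person knows the allocation.
- Limit safety conclusions to what is measured, and state that the named laboratory tests (Ca2+, ESR, hs-CRP, RF) do not support a conclusion about non-symptomatic toxicity.

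The cost is wording in the protocol and the case report form. No new visits are needed. The downside is slightly more event recording.

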### Data collection and management

2.8

The whole process of data collection and recording is carried out by one or two assistants. Personal information about potential participants and registered participants will be collected, shared and stored in a separate storeroom to protect pro-trial, in-trial and post-trial confidentiality. The access to the database will be restricted to the researchers in this study team.

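### Adverse reactions are counted only during the 4 treatment weeks, but no stated collection time falls inside them and only the needle arm has stated weekly contact, so the between-arm safety comparison may be biased

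*Protocol article*

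**What the plan says.** All references are to the protocol article.

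- **Definition (2.7).** "Adverse reactions: discomfort related to treatment occurred during treatment". Only the treatment period counts.
- **Collection times (2.7).** Adverse reactions are one item in the list of observation indexes, and one timing rule covers the whole list: "The above observation indexes are collected on the day before and after treatment". The next sentence adds follow-up: "All patients are followed up for 2 months, and the data are collected according to the same standard in the first and second month". The rule makes no distinction between arms.
- **Needle arm (2.6).** Sessions are given "Once a week for 4 weeks". During heating the operator is to keep checking with the patient: "often asking the patient how he feels to prevent scalds".
- **Control arm (2.6).** Three oral drugs, taken daily or weekly: "The patients are treated continuously for 4 weeks". No visit or call during those weeks is described, and none is excluded.
- **Blinding (2.5).** "participants and operators may be aware of random allocation"; outcome evaluators and statisticians are to be unaware.
- **Who records (2.8).** "The whole process of data collection and recording is carried out by one or two assistants".
- **Role of safety.** The abstract and the end of the introduction name efficacy and safety as the aims. Section 2.9 assigns count data to a chi-square test at P < .05.

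**The concern.** A before-and-after schedule suits a symptom score, which is a state on the day it is measured. It suits an adverse-reaction count poorly, because that count accumulates over an interval. Here the interval is the 4 treatment weeks, and the first stated enquiry after baseline comes when they are over. The month 1 and month 2 collections do not help: for events confined to the treatment period they can add only more distant recall.

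The arms also differ in their stated opportunities for an event to be noticed. Needle patients are in front of an operator every week; for control patients the article describes nothing comparable. Nothing says whether what an operator sees at a session is recorded as an adverse reaction, or whether controls are asked at matching times.

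At stake is the between-arm comparison of adverse reactions, which serves one of the trial's two stated aims. No later analysis can recover events that nobody asked about.

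**Working it through.** **1. The plan's own figure.** The only sample-size figures concern the TCM syndrome score (2.3). They are used here only as denominators.

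- Difference: 15.83 − 13.32 = 2.51.
- Pooled SD: √[(4.30² + 3.82²)/2] = 4.067.
- Standardised difference: 2.51/4.067 = 0.617.
- One-sided α = 0.025 and power 0.80 give 42.2, so 43 per group by the t test.
- With 20% withdrawal: 43/0.80 = 53.75, so 54 per group.

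The stated 43 and 54 both reproduce.

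**2. The schedules side by side.**

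| | Needle arm | Control arm |
|---|---|---|
| Period that counts | 4 treatment weeks | 4 treatment weeks |
| Stated collection times | day before, after treatment, months 1 and 2 | the same |
| Stated collection inside the 4 weeks | none | none |
| Stated contact inside the 4 weeks | weekly sessions | none stated, none ruled out |

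The third row holds on any reading. The fourth matters for the comparison only if what happens at sessions reaches the data, which gives two cases:

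- *Session events are recorded.* Needle reactions can be captured as they occur, by staff who may know the allocation. Drug reactions depend on recall or on the patient volunteering them.
- *Session events are not recorded.* Both arms rest on the same end-of-treatment enquiry, about four weeks after the earliest events.

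**3. Possible size.** The article gives no adverse-reaction rate and no capture probability, so these inputs are assumptions. Let the true rate p be the same in both arms, with capture c₁ in the needle arm and c₀ in the control arm. Observed rates are p·c₁ and p·c₀, and the spurious gap is p(c₁ − c₀).

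| True rate p | Capture c₁ v c₀ | Observed rates | Gap (points) | Ratio |
|---|---|---|---|---|
| any | equal | equal | 0 | 1 |
| 20% | 95% v 80% | 19% v 16% | 3 | 1.19 |
| 40% | 95% v 80% | 38% v 32% | 6 | 1.19 |
| 20% | 90% v 50% | 18% v 10% | 8 | 1.8 |
| 40% | 90% v 50% | 36% v 20% | 16 | 1.8 |

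**4. Chance of a false needle-arm excess.** For n per arm and a two-sided 5% test, the chance that the needle arm looks significantly worse is Φ[(gap − 1.96·SE₀)/SE₁]. SE₀ uses the pooled observed rate and SE₁ the separate rates.

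Worked for the last row at n = 54:

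- SE₀ = √(0.28 × 0.72 × 2/54) = 0.0864.
- SE₁ = √[(0.36 × 0.64 + 0.20 × 0.80)/54] = 0.0850.
- (0.16 − 1.96 × 0.0864)/0.0850 = −0.11, so Φ = 0.456.

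Across true rates of 20-40%:

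| Capture | 54 per arm | 43 per arm |
|---|---|---|
| 95% v 80% | about 6-10% | about 6-8% |
| 90% v 50% | about 22-46% | about 19-38% |

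The nominal figure is 2.5% in that direction.

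**The case against.** The strongest reply is that the written schedule is identical in both arms. Section 2.7 sets one set of times for all patients, section 2.8 has one or two assistants do all collection and recording, and nothing makes a needle session a collection point. If only the common times feed the comparison, the weekly sessions create no difference. This stands, and it is why the range starts at 0. It does not remove the other half of the point: the common schedule then leaves both arms on long recall.

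A reader might infer that the arms are in fact ascertained unequally, or that contacts number four against zero. The documents do not support either. That controls have no contact is an inference from silence, and a condensed article can leave dispensing or monitoring visits to the full protocol. Nor does it follow that a drug reaction in week 1 must stay unknown until week 4.

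The question in 2.6 about how the patient feels is a precaution against scalds during the 25-minute heating. It is not an enquiry about reactions since the last session, and it should not be read as a weekly adverse-reaction interview. It would also be wrong to say that there is a single post-treatment collection, since months 1 and 2 are scheduled.

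It can also be said that safety carries no specific hypothesis or sample size, and that bias in this direction would not flatter the new treatment. Both are fair and limit the priority. Safety remains a stated aim, however, and a distorted comparison is unhelpful in either direction.

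**Conclusion.** The point holds as a risk. On the article's own text, a count restricted to the 4 treatment weeks is collected at no time within them, and the only stated contact in those weeks is in one arm. Depending on whether session events are recorded, the result is either a comparison of observed with recalled events, probably to the needle arm's disadvantage, or loss of short-lived events in both arms.

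The size cannot be fixed from the documents. A spurious gap anywhere from 0 to 16 points is compatible with the assumptions shown: equal true rates of 20-40%, and capture ranging from equal to 90% v 50%. The sample size is unaffected. This is a cheap improvement and not a flaw that undermines the efficacy comparison.

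**What to change.** In section 2.7, take adverse reactions out of the before-and-after rule and give them their own schedule:

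1. Put one fixed set of adverse-reaction questions to both arms at the same weekly points during treatment. Ask needle patients at their session and controls by phone at the matching point, using the existing assistants.
2. Keep the post-treatment, month 1 and month 2 collections.
3. State that the between-arm comparison uses only these matched contacts. Events noticed by operators or volunteered at other times can still be recorded and listed separately.

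Cost: if the post-treatment collection serves as the last weekly point, three calls to each of 54 controls, 3 × 54 = 162 short calls, plus one form. The recorded rate of minor reactions will rise. Efficacy visits, treatment and sample size do not change.
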